## Abstract

**Background:**

Psoriatic arthritis (PsA) presents a unique clinical challenge. Affecting joints, skin, nails, and other organs, it is associated with various comorbidities and has a significant impact on quality of life, social participation and working life. While biologic and other targeted synthetic disease modifying anti-rheumatic drugs (bDMARDs and tsDMARDs) have revolutionised therapy, questions remain about the long-term safety of these agents, and their effectiveness and cost-effectiveness in the real-world clinical setting.

**Methods/design:**

The British Society for Rheumatology Psoriatic Arthritis Register (BSR-PsA) is a prospective registry of patients with PsA, recruited from across Great Britain, who are (a) commencing a bDMARD/tsDMARD; or (b) naïve to all bDMARDs/tsDMARDs. Ethical approval was given by the NHS West of Scotland Research Ethics Committee 3 (reference: 18/WS/0126). Clinical data are extracted from participants’ medical records, including symptom onset and diagnosis, joint, skin and nail symptoms, dactylitis and enthesitis. Physical measurements (height, weight and 66/68 joint counts) and a detailed drug history are taken. Participants are also asked to complete questionnaires comprising instruments relating to general health and quality of life, axial disease, sleep and fatigue, impact of disease, functional status, mental health, other symptoms, and occupational status. The study duration is 5 years in the first instance, and all participants are followed up annually until the end of the study. Participants commencing a bDMARD/tsDMARD are also followed up three and six months after the start of therapy. Disease activity, including C-reactive protein, is assessed at each visit; and participants from some centres are invited to donate blood and urine samples for the creation of a biobank.

**Discussion:**

Complementing data from randomised trials, results from this study will contribute to the evidence base underpinning the clinical management of psoriatic arthritis. Various analyses will determine the effectiveness and safety of bDMARDs/tsDMARDs in the real-world, will examine the clinical and biological predictors of treatment response, and will provide real-world data on the cost-effectiveness of these therapies, as well as providing informative data important to patients such as quality of life and occupational outcomes.

**Trial registration:**

The full study protocol is registered on the Open Science Framework (https://osf.io/jzs8n).

## Background

Psoriatic arthritis (PsA) is an inflammatory arthritis characterised by synovitis, enthesitis, osteitis, and skin and nail disease. There are several phenotypes, including oligoarticular disease, affecting only a few joints, often unilaterally; polyarticular disease, affecting five or more joints, bilaterally; and the severe and destructive, but less common, arthritis mutilans. It has a significant impact on quality of life, social participation and working life and is associated with an increased cardiovascular risk, likelihood of metabolic syndrome, and other important physical and psychological comorbidities.

The advent of TNF inhibition significantly improved outcomes for patients with PsA, and anti-TNF therapy is now established in the management of PsA [1–5]. More recently, other important targets have been identified and therapies have developed apace. Accordingly, in addition to TNF inhibitors, the rheumatologist now has access to agents that inhibit the IL-12/23, IL-17, JAK and PDE4 pathways, some of which have already demonstrated impressive results in other rheumatological diseases and/or psoriasis.

For many therapeutic agents, good quality long-term data on effectiveness, cost-effectiveness, safety, and other important outcomes in PsA are limited, and much of what is known about the performance and safety of these agents comes from clinical trials. Although these data are informative, it is often collected on a narrow subset of patients and we have shown, in axial spondyloarthritis, treatment response to biologic therapy in ‘real-world’ patients is significantly lower than is reported in clinical trials [6]. In PsA, observational ‘real-world’ evidence is needed, to complement data from randomised trials. This should seek to determine the effectiveness of treatment on all aspects of phenotype, and indeed whether treatment effectiveness varies with disease phenotype. Similarly, it is important to determine the safety and effectiveness of therapies among patients with the whole range of comorbidities seen in clinical practice, especially those that would result in ineligibility from clinical trials. Such data would allow the identification of sub-groups of patients who may have a superior treatment response, with participant numbers seldom available in randomised studies. It would also create the environment to study predictors of treatment response that might inform future stratified approaches to patient management.

All pharmacological interventions may be associated with adverse side effects. Of particular relevance, immunosuppressive therapy is considered a potential risk factor for both malignancy and life-threatening infection – although, in clinical practice, these small risks are accepted if the potential patient benefit is proportionately greater. Adverse events occurring frequently, and early during therapy, will be ascertained during phase 2 and 3 clinical trials. However, longer-term complications such as malignancy, rare infections, and indeed all rare events, are unlikely to be detected until large numbers of patients have been treated and followed for a reasonable length of time. Although much can be learned about drug safety from other disease areas, direct extrapolation from one disease to another may not be appropriate, particularly where comorbidities vary between diseases. Also, while real-world data on TNF antagonists has been available for around 20 years, much less is known about newer therapies: the IL-12/23, IL-17A, JAK and PDE4 inhibitors. Informed prescribing of new agents (and arguably new versions of old agents) requires knowledge of the magnitude of risk of adverse events in the longer-term.

Here, we describe the protocol for the British Society for Rheumatology Psoriatic Arthritis Register (BSR-PsA), a multi-centre registry facilitating research on patients with PsA, in secondary care in the Great Britain, who are commencing biologic or other targeted synthetic disease modifying anti-rheumatic drugs (bDMARDs and tsDMARDs), plus a comparison cohort of patients naïve to bDMARD / tsDMARD therapy. It aims to provide high quality long-term data on effectiveness, cost-effectiveness, safety, and the impact of PsA on the individual, including function, quality of life and social (e.g. work) outcomes in the medium- to long-term. It also collects the relevant data to allow robust health economic evaluation and post-marketing surveillance of biologic and other targeted therapies for a period beyond that typically monitored in clinical trials.

## Methods/design

### Study design, population, and procedures

The BSR-PsA is a multi-centre registry of persons aged ≥16 yrs with a clinical diagnosis of PsA and who meet the CASPAR classification criteria for PsA [7]. They are also required to be either:
Commencing a biologic, biosimilar or targeted synthetic disease modifying anti-rheumatic drug (bDMARD or tsDMARD) approved for the treatment of PsA in the United Kingdom or part thereof, having never previously received that particular agent; orNaïve to all bDMARD and tsDMARD products.

Thus, the registry comprises two cohorts, considered ‘exposed’ and ‘non-exposed’ respectively. Participants are excluded if they are unable to communicate in English; are managed in paediatric rheumatology services; are remaining on, or restarting, a bDMARD or tsDMARD that they have previously received; or are unable to give informed consent. The registry inclusion / exclusion criteria are shown in Table 1.

**Table 1 Tab1:** Registry inclusion / exclusion criteria

Inclusion criteria	Exclusion criteria
**• Patients must …**	**• Patients must not be …**
**•** Have a clinical diagnosis of PsA;	Unable to communicate in English;
**•** Meet CASPAR classification criteria for PsA [7];	Deemed, in any other way, unable to give informed consent;
**•** Be aged ≥16 years;	Managed in paediatric rheumatology services;
**•** Be either:	Currently taking a bDMARD / tsDMARD and not changing treatment;
(a) Naïve to all bDMARD / tsDMARD agents; or	Restarting a specific bDMARD / tsDMARD agent that they have received previously^a^.
(b) Starting a bDMARD / tsDMARD agent, approved for the treatment of PsA in the United Kingdom, having never previously received that particular drug^a^.	

^a^Patients are eligible if they are starting, or switching to, a biosimilar product even if they have previously had (i) the originator product, and/or (ii) a different biosimilar of the same product

Potentially eligible patients with PsA are identified from participating NHS rheumatology departments across the UK. A list of participating centres is available from www.abdn.ac.uk/bsr-psa. Patients are sent a participant information sheet and invitation letter from their usual rheumatology consultant/team ahead of their clinic appointment. Thereafter, at clinic, they are asked whether they wish to participate. Recruitment is supported in England by the National Institute for Health Research (NIHR) Clinical Research Network, and elsewhere in the UK equivalent research infrastructure support is available. Participant recruitment commenced in September 2018 and is currently ongoing.

Participant eligibility is confirmed by the consultant rheumatologist or a suitably qualified member of the local research team with delegated responsibility from the local Principal Investigator. Being an observational study, cohort membership (i.e. whether the participant joins the exposed or non-exposed groups) is not dictated by the study protocol. Rather, it is determined by the treatment decision of the rheumatology consultant, and the patient, as per usual clinical practice.

Patients have at least 24 h to consider the information in the participant information sheet and have the opportunity to ask questions. However, in line with the ethical approval, if they indicate their willingness to participate sooner, the taking of consent is not unduly delayed. Although the majority of recruitment takes place face-to-face, in exceptional circumstances participants may complete the consent form and return it by post, providing that the local research nurse has had an opportunity (either face-to-face or by telephone) to discuss the study with the participant, and to answer any questions.

### Data collection

During the development of the protocol and data collection procedures, a consultation meeting was held with representation from study investigators, patients, and rheumatology consultants, to ensure that data collection was relevant and comprehensive but avoided duplication.

There are three main aspects of data collection.
Clinical data

Data are recorded on a variety of clinical features, either directly assessed by the research nurse or taken retrospectively from the clinical notes, and includes information regarding:
Symptom onset and diagnosis;Joint disease;Skin and nail disease;Dactylitis;Enthesitis; andComorbidities.

Training was provided for research nurses prior to commencement of the study. Various physical measurements and laboratory test results are also taken. A full list of clinical data collection items is shown in Table 2. In addition, during follow-up, clinical staff are asked to report any significant morbid events as well as being asked to verify any such events notified in patient diaries. Safety reporting is discussed below.
(b)Patient-reported data

**Table 2 Tab2:** Clinical data collection

Domain	Items
General information	Date of birth; gender; ethnicity; family history of PsA, psoriasis, and other relevant conditions.
Symptom onset and diagnosis	Age at onset for joint disease, and skin disease, separately. Year that patient was first seen in rheumatology.
Joint disease	66/68 joint count.
Skin disease severity/phenotype	Personal history of psoriasis. Current psoriasis: (a) phenotype: plaque, pustular (sub classified as palmoplantar pustulosis or generalised pustular psoriasis); and (b) severity: body surface area affected, static physician global assessment.
Nail disease	Presence of nail disease: nail matrix (e.g. pitting); nail bed (e.g. onycholysis); hyperkeratosis.
Dactylitis	Current swelling of an entire digit; count of involved digits; history of dactylitis.
Enthesopathy	Leeds Enthesitis Index [8].
Physical measurements	Height; weight; waist circumference; and blood pressure.
Comorbidities	Diabetes; ischaemic heart disease; hypertension; hyperlipidaemia; statin use; fatty liver disease; history of malignancy; history of serious infection (infection resulting in hospitalisation, intravenous antibiotics); history of vasculitis; mental health.
Novel therapy exposure	Past history of all bDMARDs and tsDMARDs, including start date, dose, stop date and reason for discontinuation.
Other current and recent therapies	History of conventional synthetic DMARDs, steroids, NSAIDs, PUVA, and systemic therapies for psoriasis. Data recorded will comprise ever received therapy (yes/no); and, if applicable, calendar year. A recent history (past 6 months) will also be taken, comprising start date, dose, and if applicable, stop date and reason for discontinuation. Information will also be collected on any relevant concomitant therapies for comorbidities.
Spinal involvement/imaging	Evidence of (a) juxta-articular new bone formation; (b) any erosion; and/or (c) sacroiliitis, by plain x-ray or MRI. (NB: No new images will be taken specifically for the BSR-PsA.)
Laboratory markers	Recent measure of inflammation (C-reactive protein) from the date of clinic visit date ±4 weeks. Baseline only: rheumatoid factor and anti-citrullinated protein (anti-CCP) antibody, if available.

At baseline and each follow-up point participants are asked to complete a questionnaire. A full list of questionnaire instruments is shown in Table 3 and includes questions on:
General health;Functional status and impact of disease;Axial disease;Sleep and fatigue;Fibromyalgia;Mental health;Quality of life; andEmployment status.

**Table 3 Tab3:** Patient-reported data collection

Domain	Items
General information	Date of birth; education; smoking status, alcohol consumption; and physical activity.
General health	PROMIS Scale v1.2 – Global Health [9]; and GRAPPA/OMERACT visual analogue scales (global, skin and joints) [10].
Axial disease	Bath Ankylosing Spondylitis Disease Activity Index (BASDAI) [11].
Sleep, Fatigue and Fibromyalgia	Jenkins Sleep Scale [12]; PROMIS Short Form – Fatigue 8a [9]; a general question on fatigue for comparability with other studies (have you had problems with fatigue for more than 3 months?); plus, the 2011 modification of the ACR preliminary diagnostic criteria for fibromyalgia [13].
Quality of life, and Impact of disease	Generic instrument (EQ-5D-5L) [14]; plus, the PsA Quality of Life (PsAQoL) [15]; Dermatology Quality of Life Index (DLQI) [16]; and Psoriatic Arthritis Impact of Disease (PsAID) questionnaire [17].
Functional status	Health Assessment Questionnaire (HAQ) [18].
Mental health	PROMIS Short Form – Anxiety 4a and Depression 4a questionnaires [9] plus, for comparability with other studies, a question on anhedonia taken from the PHQ-9 [19].
Employment status	Employment status, and the impact of PsA on employment: Work Productivity and Activity Impairment Questionnaire: Specific Health Problem (WPAI: SHP) [20].

At baseline, participants are also asked for their preference – postal, or online – which determines the approach for follow-up questionnaires.
(iii)Record linkage

Participants are asked for their consent to link their study data to records held by NHS Digital (www.digital.nhs.uk) for surveillance and notification of any malignancy and/or mortality. In addition, for persons recruited in Scotland data are linked to the Scottish Morbidity Records held by National Health Services Scotland (www.ndc.scot.nhs.uk), providing information on inpatient episodes (including day case) and outpatient attendances.

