### Follow-up

The study duration is 5 years in the first instance, and all participants are followed up annually until the end of the study, unless they withdraw. In addition, patients commencing or switching to bDMARD or tsDMARD therapy (either at recruitment, or during the course of the study) will be followed up three and six months after the start of therapy. Ordinarily, recruiting centres endeavour to ensure that each follow-up visit takes place within ±28 days of the required time.^1^ Each follow-up visit involves the collection of clinical and patient-reported data, as per baseline. To decrease the burden for recruiting centres, follow-up data collection is designed to collect clinical data using a schedule that maps to usual clinical practice insofar as possible, although data collection can also take place at additional study-specific visits.

During follow-up participants are asked to keep diaries to record any hospital admissions, new drugs prescribed, new referrals and/or pregnancy. In female participants, in the event of a pregnancy, a supplementary questionnaire is sent, shortly after the expected date of delivery, to collect information about the pregnancy, and pregnancy outcome. If a pregnancy is reported in a study participant's partner, the questionnaire is sent to the participant to pass on to their partner, with a separate participant information sheet and consent form.

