### Biobank

Recent evidence suggests that different PsA phenotypes may be determined by distinct genotypes and cytokine responses [22]. This gives rise to specific testable hypotheses about treatment response among patients receiving therapeutic agents that ostensibly target single pathways. Not available from the start of the study, but beginning in 2021, we will collect and store urine, serum, and plasma from a sub-sample of participants to create a PsA biobank which will facilitate analyses at the genomic, epigenetic, transcriptomic (including non-coding RNA species) and metabolomics level.

Depending on local facilities, participants commencing bsDMARD or tsDMARD therapy (either at recruitment, or during follow-up) will be given the option of contributing to a biobank. Those who consent will be asked to give blood and urine samples at their normal clinical visit when commencing therapy, and at three-month follow-up. Blood samples will be centrifuged in local facilities and plasma and serum extracted, and samples will be transferred to the NHS Grampian Biorepository where they will be stored for up to 10 years.

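### The ±4-week C-reactive protein window also applies at baseline, so in participants starting a bDMARD/tsDMARD a value taken after the first dose can count as baseline

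*Protocol article*

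**What the plan says.** The laboratory row of Table 2 (Protocol article, Data collection) gives one timing rule for CRP: "Recent measure of inflammation (C-reactive protein) from the date of clinic visit date ±4 weeks". In the same row rheumatoid factor and anti-CCP are restricted to baseline, but CRP is not. The Abstract confirms that it is measured throughout: "Disease activity, including C-reactive protein, is assessed at each visit". The one rule therefore covers the baseline visit and every later visit.

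The exposed cohort is defined by a treatment start (Study design, population, and procedures): "Commencing a biologic, biosimilar or targeted synthetic disease modifying anti-rheumatic drug (bDMARD or tsDMARD) approved for the treatment of PsA". The Follow-up section adds 3- and 6-month visits after a start, which may occur "either at recruitment, or during the course of the study". Centres "endeavour to ensure that each follow-up visit takes place within ±28 days of the required time".

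For the main data set, the article does not say how the baseline visit date relates to the first dose. The nearest text is in the Biobank section, where consenting participants "give blood and urine samples at their normal clinical visit when commencing therapy, and at three-month follow-up". Drug history is collected in a form that includes start dates: "Past history of all bDMARDs and tsDMARDs, including start date, dose, stop date and reason for discontinuation".

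**The concern.** A baseline measurement should describe the patient before treatment. A window that extends four weeks past the visit does not guarantee this when the visit is the occasion for starting therapy. The word "recent" might suggest a look back, but the ± sign expressly admits later values. Clinical data may also be taken retrospectively from the notes, so a blood test dated after the visit can readily be entered.

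If treatment lowers CRP early, a post-start value makes the starter's disease look less inflamed than it was. CRP is the only inflammation marker listed in Table 2. The planned work includes a baseline comparison of exposed and non-exposed groups, adjustment for differences between them, and study of predictors of response. Wherever CRP enters these analyses, three effects would follow: initial severity in starters is understated, change from baseline shrinks, and some early responders look like patients who began with low CRP.

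A second, smaller issue comes from the same rule. The CRP window sits on top of a visit window of equal width, so one blood test may qualify for two consecutive visits.

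**Working it through.** The plan states no figure for this point, so there is nothing to reproduce. The check is date arithmetic followed by an illustration of size.

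**Inputs.** From the article: CRP window ±4 weeks (28 days) around the visit (Table 2); visit window ±28 days around the due date (Follow-up); 3- and 6-month visits counted from the start of therapy (Follow-up). Conventions: 3 months = day 91, 6 months = day 183. Assumed, because the article gives neither: the share *f* of starters' baseline CRPs taken after the first dose, and the fraction *r* by which CRP has fallen by then.

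**1. Share of the baseline window after the start.** Let *s* = date of first dose minus date of baseline visit, in weeks. Measured from the first dose, the window runs from −4 − *s* to 4 − *s*. The post-start share is the part above 0 divided by 8.

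| First dose relative to visit | Window relative to first dose (weeks) | Post-start share |
|---|---|---|
| 4 weeks after visit | −8 to 0 | none |
| 2 weeks after visit | −6 to +2 | 1/4 |
| same day | −4 to +4 | 1/2 |
| 2 weeks before visit | −2 to +6 | 3/4 |
| 4 weeks before visit | 0 to +8 | all |

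In whole days, the same-day case is 28 of 28 + 1 + 28 = 57 days, or 49%.

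**2. Possible effect on baseline CRP.** If a share *f* of values is multiplied by (1 − *r*) and the rest are unchanged, the geometric mean is multiplied by (1 − *r*)^*f*.

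- *f* = 5%, *r* = 25%: 0.75^0.05 = 0.99 (about 1% too low)
- *f* = 10%, *r* = 50%: 0.50^0.10 = 0.93 (about 7% too low)
- *f* = 25%, *r* = 50%: 0.50^0.25 = 0.84 (about 16% too low)
- *f* = 50%, *r* = 75%: 0.25^0.50 = 0.50 (50% too low)

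**3. Overlap between visits.**

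- With visits on their due dates, the CRP windows are days 91 ± 28 = 63 to 119 and 183 ± 28 = 155 to 211. They do not overlap.
- With the visit window added, the limits are 91 ± 56 = days 35 to 147 and 183 ± 56 = days 127 to 239. They overlap on days 127 to 147.
- One sample can serve both visits only if the visits are at most 28 + 28 = 56 days apart. They are due 183 − 91 = 92 days apart, so they must drift towards each other by at least 92 − 56 = 36 days in total. The most the visit window allows is 56.
- If both visit dates were independent and uniform over ±28 days (assumed), this would occur with probability (56 − 36)² / (2 × 56²) = 400 / 6272, about 6%.
- In the extreme, with visit and first dose on the same day, a baseline CRP on day 28 and a 3-month CRP on day 35 are one week apart.

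**The case against.** The strongest reply is that this is a condensed article. The full protocol is registered elsewhere and is not shown, it may already require a pre-dose value, and every analysis is to have its own plan specified in advance. Start dates are collected, and a ±4-week rule can be applied only if the sample date is known, so a later plan could drop post-start values. This carries weight but does not dispose of the point. The article states a symmetric rule; it is not merely silent. The rule governs data capture: if a post-start value is entered where a pre-start one was available, no analysis plan can bring the earlier value back. Sample date is not among the items listed in Table 2, though the full protocol may include it.

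A symmetric window is also a sensible, pragmatic choice for a registry that follows usual care. That stands for follow-up visits and for participants not starting therapy.

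A reader might go further and infer that the rule biases baseline disease activity in the exposed cohort only, by up to four weeks of treatment. The documents do not support that:

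- The four-week limit holds only if visit and first dose coincide, which is not stated.
- The window is given for CRP alone, not for joint counts, skin, enthesitis or questionnaires.
- Participants who start therapy later face the same problem at whichever visit serves as their pre-treatment reference. Non-exposed participants may change conventional DMARDs or steroids around a visit, so how differential the error is cannot be shown.
- The example models in Statistics and data analysis (serious infection; minimal disease activity at twelve months) do not name CRP.

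**Conclusion.** The point holds as a weakness in a stated data-collection rule. As written, the rule accepts a CRP taken after the first dose as baseline in participants starting a bDMARD/tsDMARD, whether at recruitment or later. The direction is clear if treatment lowers CRP within weeks: pre-treatment inflammation in starters would tend to be understated wherever CRP is used for baseline comparison, confounder adjustment, change or prediction of response.

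The size is not known. The 49% applies only to a same-day start, and the 1% to 50% range rests entirely on assumed values of *f* and *r*. It shows that the effect could be trivial or substantial, not that bias has occurred. The overlap between the 3- and 6-month windows is real but needs at least 36 days of combined visit drift, so it is a secondary matter. Overall this is a cheap improvement, not a flaw that undermines the register.

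**What to change.** In the CRP row of Table 2 (and in the full protocol, if it does not already say so), add a rule for participants starting a bDMARD/tsDMARD, at recruitment or during follow-up:

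1. Baseline CRP is a value dated on or before the first dose and within the preceding 4 weeks.
2. The sample date of every CRP is recorded.
3. A value dated after the first dose is not baseline. It is either set to missing at baseline or kept and flagged.
4. Each CRP value is assigned to one visit only, the nearest in time.

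The ±4-week window can stay for follow-up visits. The change costs one line in the data-collection table and one analysis rule, and start dates are already in the drug history. As recruitment was described as ongoing, it would still benefit later entrants. For participants already enrolled, rules 3 and 4 can be applied retrospectively where sample dates exist. The downside is that some starters will have no valid baseline CRP. Flagging rather than deleting later values keeps them available for sensitivity analysis.
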